### Study design

2.1

This is a three-arm superiority randomised controlled trial (RCT) that evaluates the impact of two types of incentives against a control condition on willingness to participate in EMA research among an urban neighbourhood population.

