### Sample size

2.4

The sample size for this study was fixed at 4,809 individuals, representing the total number of users in the King's Cross Equiem database who met the eligibility criteria. Power analysis was conducted to evaluate the study's ability to detect differences between the three incentive conditions under varying levels of willingness to participate in the control group. Because the total N was fixed by the sampling frame, results are presented as minimum detectable differences (MDEs) in percentage points for each assumed control rate (29). Power for differences in proportions was calculated using standard two-sample methods for binary outcomes (30).

Due to limited directly comparable external estimates of baseline participation without incentives in similar digital-based recruitment contexts, a plausible range of control proportions (1%–70%) was assumed and used as a sensitivity analysis. Because EMA recruitment can yield single-digit participation rates in some settings (23), MDEs for low baseline proportions (1%–10%) are included within this range as part of the same fixed-N sensitivity framework. Power calculations were then conducted for each assumed proportion, using a Bonferroni-adjusted significance level of 0.01667 (0.05/3) to maintain a family-wise error rate of 0.05 across the three planned pairwise comparisons among the three conditions (31). Table 2 summarizes the assumptions and the corresponding minimum detectable differences.

**Table 2 T2:** Results of power analysis for detecting differences in willingness to participate across incentive conditions.

N	Proportion willing in control	Percentage point difference
4,809	0.01	1.16
4,809	0.02	1.53
4,809	0.03	1.81
4,809	0.04	2.04
4,809	0.05	2.24
4,809	0.06	2.41
4,809	0.07	2.57
4,809	0.08	2.72
4,809	0.09	2.85
4,809	0.10	2.97
4,809	0.20	3.86
4,809	0.30	4.36
4,809	0.40	4.61
4,809	0.50	4.66
4,809	0.60	4.52
4,809	0.70	4.18

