With a fixed sample size of 4,809 and using the adjusted alpha for planned pairwise comparisons described above, the study would have approximately 80% power to detect absolute differences in willingness to participate of a few percentage points, depending on the assumed control proportion (Table 2). For example, if 30% of individuals in the control group were willing to participate, there would be sufficient power to detect an increase of 4.36 percentage points, corresponding to a willingness rate of 34.36% in an incentive condition. By contrast, if baseline willingness is in the single-digit range, detecting smaller absolute increases (e.g., 2 percentage points) with 80% power at *α* = 0.01667 would require a substantially larger sample per group than was available under the fixed sampling frame. These MDE benchmarks will be used to interpret observed effects under the predetermined sampling frame. If baseline willingness is in the single-digit range, smaller absolute effects may not be detected reliably; accordingly null findings will be interpreted relative to the corresponding low-rate MDE. These detectable differences provide a transparent benchmark for interpreting effects under the predetermined sampling frame.

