#### Sequence generation

2.7.1

Participants were randomized into three incentive groups (financial incentive, non-financial incentive, or no incentive) using a stratified block randomization procedure. Stratification was based on participant type within the Equiem communication platform (residents, visitors, and commercial occupiers). Randomization lists were generated using the Sealed Envelope online randomization service, which employed randomly permuted block sizes of 3, 6, and 9 to ensure a balanced allocation across incentive groups within each stratum. Sealed Envelope is a web-based clinical trial randomization platform that generates allocation sequences based on user-specified parameters (e.g., allocation ratio, stratification variables, and randomly permuted block sizes) and allows the sequence to be exported for implementation (33). The platform provides documentation on permuted-block and stratified randomization procedures, supporting transparent reporting and reproducible sequence generation. The randomization lists were generated by the researcher prior to participant assignment and without access to any identifying information (e.g., names or email addresses) stored on the Equiem platform.

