#### Primary outcome analysis

2.12.1.

The primary outcome is willingness to participate (Yes/No), operationalized as submission of a completed core questionnaire and valid email address (“Yes”) vs. not registering interest (selecting the non-interest option or not selecting either option). The effect of incentive type (financial, social, or no incentive) on willingness to participate will be evaluated using logistic regression. The model will include incentive condition as the main predictor and residential status (residents, workers, visitors) as a covariate, consistent with the stratification used during randomization. Odds ratios (OR) with 98.33% confidence intervals (CI) will be reported to compare each incentive group with the control group. A two-tailed *p*-value of < 0.01667 will be considered statistically significant (Bonferroni-adjusted to control the family-wise error rate at 0.05 across the three planned pairwise comparisons). In addition to odds ratios, marginal risk differences (RD) will be estimated to enhance interpretability.

Predicted probabilities will be obtained from the fitted logistic model through marginal standardization and RDs will be computed as the absolute difference in these marginal probabilities between groups. Confident Intervals (95%) will be derived using robust standard errors or nonparametric bootstrap methods, as appropriate. Primary inferences for the three pairwise comparisons of incentive type on the primary outcome will use 98.33% confident intervals (CIs) to adjust for multiple comparisons. Exploratory subgroup analyses and complementary RD estimates use 95% CIs and will be interpreted as estimation rather than confirmatory hypothesis testing. Interaction terms in subgroup models will be evaluated at a two-tailed alpha level of 0.05 and results will be reported as exploratory findings. In addition to the frequentist primary analysis, Bayes factors will be calculated to complement interpretation of the primary outcome by quantifying evidence for differences between incentive conditions.

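### The detectable differences in Table 2 fit two arms of about 2,404, not three of 1,603, so power at the stated differences is about 60% per comparison, not 80%

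*Protocol article*

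**What the plan says.** **Design.** Section 2.1 states: "This is a three-arm superiority randomised controlled trial (RCT". In section 2.4: "The sample size for this study was fixed at 4,809 individuals". Section 2.7.1 describes "randomly permuted block sizes of 3, 6, and 9 to ensure a balanced allocation across incentive groups within each stratum".

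**Power calculation.** Section 2.4 explains: "Because the total N was fixed by the sampling frame, results are presented as minimum detectable differences (MDEs) in percentage points". It names standard two-sample methods for binary outcomes, "using a Bonferroni-adjusted significance level of 0.01667 (0.05/3) to maintain a family-wise error rate of 0.05 across the three planned pairwise comparisons". Section 2.12.1 fixes the sidedness: "A two-tailed *p*-value of < 0.01667 will be considered statistically significant". Table 2 lists the total N, an assumed control proportion and a detectable difference; it has no per-arm column.

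**Claims drawn from it.** Section 2.4 puts power at roughly 80% for the tabulated differences. Its example is a 30% control rate, where "there would be sufficient power to detect an increase of 4.36 percentage points, corresponding to a willingness rate of 34.36% in an incentive condition". It adds that, at single-digit control rates, detecting smaller gains such as 2 points "would require a substantially larger sample per group than was available under the fixed sampling frame". It then makes the tabulated values the benchmark for reading observed effects and null results.

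**The concern.** Each planned test compares two of the three arms, so a detectable difference depends on the number in those two arms and not on the total. A third of 4,809 is 1,603. The printed differences look too small for that number at the stated alpha and power.

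N was fixed by the sampling frame and the trial has ended, so no recruitment decision turns on this. What is at stake is the claim about sensitivity. If a null finding at a 5% control rate is read as having had 80% power against 2.24 points, when power was about 60%, the report overstates what the trial can rule out. The article itself regards single-digit rates as plausible, and it says null findings there will be judged against these values.

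**Working it through.** **Inputs**
- Total N = 4,809 (section 2.4).
- Three arms (section 2.1). Allocation taken as 1:1:1 from the balanced blocks of 3, 6 and 9 (section 2.7.1), so n = 4,809/3 = 1,603 per arm.
- Two-sided alpha = 0.05/3 = 0.01667 (sections 2.4 and 2.12.1), so z = 2.394.
- Power 80% (section 2.4), so z = 0.842.
- No allowance for attrition: all randomised invitees are analysed and non-responders count as not willing (sections 2.9.1 and 2.12).

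**Formula.** With control rate p1, incentive rate p2 = p1 + d and their mean p̄,

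power = Φ{ [d − 2.394·√(2p̄(1−p̄)/n)] / √([p1(1−p1) + p2(1−p2)]/n) }.

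The minimum detectable difference is the d that gives 0.80.

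**Step 1: reproduce the printed figure.** Take p1 = 0.30, p2 = 0.3436, d = 0.0436, p̄ = 0.3218.
- n = 4,809/2 = 2,404.5: the null standard error is 0.01347 and the alternative 0.01346. (0.0436 − 2.394 × 0.01347)/0.01346 = 0.843, so power is 80.0%. This is the article's figure.
- n = 1,603: the standard errors are 0.01650 and 0.01648. (0.0436 − 2.394 × 0.01650)/0.01648 = 0.248, so power is 59.8%.

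**Step 2: all rows** (percentage points, 80% power).

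| Control rate | Table 2 | n = 2,404.5 | n = 1,603 |
|---|---|---|---|
| 1% | 1.16 | 1.16 | 1.50 |
| 2% | 1.53 | 1.53 | 1.94 |
| 3% | 1.81 | 1.81 | 2.28 |
| 4% | 2.04 | 2.04 | 2.55 |
| 5% | 2.24 | 2.24 | 2.80 |
| 6% | 2.41 | 2.41 | 3.01 |
| 7% | 2.57 | 2.57 | 3.20 |
| 8% | 2.72 | 2.72 | 3.38 |
| 9% | 2.85 | 2.85 | 3.54 |
| 10% | 2.97 | 2.97 | 3.69 |
| 20% | 3.86 | 3.86 | 4.76 |
| 30% | 4.36 | 4.36 | 5.36 |
| 40% | 4.61 | 4.61 | 5.65 |
| 50% | 4.66 | 4.66 | 5.70 |
| 60% | 4.52 | 4.52 | 5.52 |
| 70% | 4.18 | 4.18 | 5.10 |

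Every row matches at 2,404.5 per group and none at 1,603. Solving each printed row for n gives 2,396 to 2,418 per group. At 1,603 per arm, power at the printed differences lies between 59.5% and 60.0%. The ratio of correct to printed value runs from 1.22 (70%) to 1.29 (1%).

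**Step 3: could another setting give 4.36 with 1,603 per arm?** At a 30% control rate:
- two-sided 0.05: 4.63
- one-sided 0.01667: 4.91
- one-sided 0.05: 4.10
- continuity correction at two-sided 0.01667: 5.42
- control against both incentive arms pooled (1,603 versus 3,206): 4.64 at 0.01667, 4.01 at 0.05

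None does. An arcsine calculation at two-sided 0.01667 gives 59.9% power for 30% versus 34.36%. Dropping the Bonferroni adjustment raises power for that contrast only to about 75%.

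**Step 4: the 2-point remark.** The n per arm needed for a 2-point gain at alpha 0.01667 and 80% power is 1,025 at 1%, 1,522 at 2%, 2,009 at 3% and 2,951 at 5%. Against 1,603 available, 2 points is detectable at 1% and 2% but not from 3% upward; the crossover is near 2.2%. Table 2 as printed also contradicts the remark, since it shows values below 2 at 1%, 2% and 3%.

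**The case against.** The article prints no per-arm n and does not write out the allocation ratio, so both the 1:1:1 split and the two-group cause are inferred. That is fair, and the cause is best described as what the figures are consistent with. It does not rescue the figures: with three arms, no allocation puts about 2,404 people in each of two arms without leaving the third almost empty.

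The reach of the error is also limited. The primary analysis rests on the logistic model, the 0.01667 threshold, 98.33% intervals, risk differences and Bayes factors, none of which uses Table 2. No estimate, test or interval changes. What remains affected is the 80% power claim and the benchmark for reading results, a use that the article plans explicitly.

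On the 2-point remark, the article offers 2 points as an illustration. At the correct n the remark is true for seven of the nine single-digit rows (3% to 9%). It needs a qualification and is a minor matter beside Table 2.

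**Conclusion.** The concern holds. With three balanced arms of 1,603, two-sided alpha 0.01667 and an unadjusted two-proportion test, the trial has about 60% power per pairwise comparison at each difference in Table 2, not 80%. The correct detectable differences are 22% to 29% larger than printed: for example 2.80 rather than 2.24 points at 5%, and 5.36 rather than 4.36 at 30%. Detecting 4.36 points from 30% would take 2,403 per arm, or 3 × 2,403 = 7,209 in all. The result assumes near-equal allocation; imbalances of a few people from incomplete blocks would not alter it. That the total N went into a two-group calculation is an inference, but it accounts for all 16 rows. The figures must be corrected because the article makes them its yardstick for null findings.

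**What to change.** In section 2.4:
- Replace the difference column of Table 2 with the n = 1,603 values above, and add a column for n per arm.
- State the 1:1:1 allocation, and say that the 80% power applies to each pairwise comparison at two-sided alpha 0.01667.
- Change the worked example to 30% versus 35.36%, an increase of 5.36 points.
- Reword the 2-point remark: an increase of 2 points is detectable at control rates up to about 2%, and not from about 3% upward.

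Use only the corrected values wherever minimum detectable differences are cited in the results paper or the analysis plan. Since the data have been collected, label the change as a correction of an arithmetic error and give its date.

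The cost is a correction to text and one table. The stated sensitivity becomes less favourable. Conduct, data and the primary analysis are unchanged.

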### Recruitment

2.5

The three groups of participants: commercial occupiers, residents, and visitors to Kings Cross are recruited from a neighbourhood mobile application with registered users. The participants could consequently be considered as a self-selected subsample of the neighborhood's population. The mobile application is the King's Cross Community App, and it is available on Android through Google Play and iPhone through the App Store (32). It is used to share information about the neighbourhood salons, bars, shops, and restaurants, in addition to relevant deals, offers, events, and ticket giveaways in the neighbourhood. The app is informational and does not support peer-to-peer communication (e.g., user posts or direct messaging), and users cannot view or identify other registered users. Table 3 presents the composition of the three groups of participants to be recruited in the mobile app.

**Table 3 T3:** Total composition of king's cross community mobile application users.

Group	Total app users	Recruited no.	Recruited no. (%)	Total recruited (%)
Commercial Occupiers (Office & Retail)	3,869	1,172	30.29	24.37%
Residents	1,208	541	44.78	11.25
Public (Visitors)	11,176	3,096	27.7	64.38
Total	16,253	4,809		100

The King's Cross mobile app is owned by The King's Cross Group, a UK property developer specializing in mixed use development with a focus on placemaking and regeneration. This urban regeneration specialist has led the regeneration of King's Cross for more than two decades and remains the asset manager for the neighbourhood. The application is managed by Garden State London—a marketing and digital communications agency company—to disseminate latest information about the neighbourhood to registered users on the app and emails. Study invitations and intervention emails were distributed to registered users via email (rather than being posted within the app), and no study-related content was shared through the app interface. The agency is responsible for recruiting participants for this study and delivering the study intervention to eligible participants following the participant eligibility criteria and other guidelines provided by the study authors.

### Trial flow

2.6

The trial commenced on September 12, 2024, and ended on November 30, 2024. Participants in different neighbourhood strata received randomized emails simultaneously (Figure 1). The initial email was disseminated on September 12, 2024, and the participation survey link remained open until November 30, 2024. A single follow-up (reminder) email was disseminated one month later (October 17, 2024).

**Figure 1 F1:**
[figure not shown]
Schedule of enrolment, allocation, invitation delivery, reminder, and outcome ascertainment. **Note**. All invitees had previously consented to receive email communications during sign-up for the community app or the King's Cross website email newsletter. Additional informed consent for study participation was obtained at questionnaire entry before any survey items were answered. Reminder emails were sent only to nonresponders.

### Randomization

2.7

#### Sequence generation

2.7.1

Participants were randomized into three incentive groups (financial incentive, non-financial incentive, or no incentive) using a stratified block randomization procedure. Stratification was based on participant type within the Equiem communication platform (residents, visitors, and commercial occupiers). Randomization lists were generated using the Sealed Envelope online randomization service, which employed randomly permuted block sizes of 3, 6, and 9 to ensure a balanced allocation across incentive groups within each stratum. Sealed Envelope is a web-based clinical trial randomization platform that generates allocation sequences based on user-specified parameters (e.g., allocation ratio, stratification variables, and randomly permuted block sizes) and allows the sequence to be exported for implementation (33). The platform provides documentation on permuted-block and stratified randomization procedures, supporting transparent reporting and reproducible sequence generation. The randomization lists were generated by the researcher prior to participant assignment and without access to any identifying information (e.g., names or email addresses) stored on the Equiem platform.

#### Concealment mechanism and implementation

2.7.2

The randomization sequence was generated by the principal researcher using Sealed Envelope prior to data collection, exported, and stored securely in Microsoft Excel. The list was shared with only two authorized Garden State staff members who had controlled access to the Equiem platform where participant details were stored

Allocation was implemented sequentially by a designated Garden State staff member who matched each participant's email address to the next available group assignment on the pre-generated randomization list. This was performed directly within the Equiem platform interface, where participants' names and emails were visible only during assignment. The staff followed the randomization list exactly, without alteration or discretion.

To maintain allocation concealment and independence of implementation, the principal researcher did not have access to participant identifiers (including email addresses) or the allocation list at any point during the assignment process. Upon completion of assignment (and prior to email dissemination), a second Garden State staff member independently verified the accuracy of allocations by cross-checking the final participant–group assignments against the original Sealed Envelope list (e.g., confirming each participant's assigned group corresponded to the correct sequence position).

#### Binding

2.7.3

Blinding of participants and implementation staff was not feasible due to the nature of the intervention and the manual assignment process within the Equiem platform. Each participant received an email corresponding to their assigned incentive condition (financial, social, or control) and thus was aware of their own allocation. However, participants were not informed that alternative incentive options existed, which helped to minimize offline cross-group contamination. Emergency unblinding procedures were not applicable, as participants were aware of their assigned condition upon receiving the email invitation and there were no concealed allocations to unblind.

Awareness of other incentive conditions could have influenced participants' willingness to participate. For instance, participants in the control group might have been less inclined to engage if they knew others were receiving financial incentives. To reduce this potential source of bias, participants were asked at the beginning of the questionnaire to keep their study participation and incentive details confidential until contacted by the research team (see Supplementary File S1). This request was particularly relevant in shared work environments where colleagues might have received different email interventions.

Although allocation blinding was not possible, allocation concealment was maintained until the point of assignment, as the randomization sequence was inaccessible to both participants and platform staff prior to implementation. During data analysis, participant identifiers would be pseudonymized to ensure objectivity and minimize any potential bias in outcome assessment.

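### Allocation was not concealed from the platform staff member who assigned users, although the protocol says it was, and the verification described could not detect any reordering of users within a stratum

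*Protocol article*

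**What the plan says.** Section 2.7.3 (printed as Binding) concedes that participants and implementing staff could not be blinded. It then states that concealment was kept up to assignment, on the ground that "the randomization sequence was inaccessible to both participants and platform staff prior to implementation".

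Section 2.7.2 gives the procedure. The sequence was produced in advance and exported to a spreadsheet. "The list was shared with only two authorized Garden State staff members who had controlled access to the Equiem platform where participant details were stored". One of these staff "matched each participant's email address to the next available group assignment on the pre-generated randomization list". This was done in the platform interface, "where participants' names and emails were visible only during assignment". The section adds that staff kept to the list with no changes and no room for judgement. After assignment and before mailing, the second staff member compared the final assignments with the list. The example given of that check is that each person's group agreed with its place in the sequence.

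Section 2.7.1 gives randomly varying blocks of 3, 6 and 9 within three strata. Section 2.4 says the trial took in every eligible user on the platform, 4,809 in all.

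**The concern.** Concealment means that whoever places a person in the sequence does not know the coming allocation. Here that person held the whole list and could see who was being placed. Random block sizes hinder guessing, but they do nothing against someone who can read the list. The remaining protection is an order of users settled before the list was opened, and the article does not say there was one.

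What is at stake is the protection the trial may claim. Section 2.12 commits to CONSORT reporting, so the sentence in Section 2.7.3 would be carried forward as a safeguard that the described procedure lacks. The planned data also offer little chance to see an imbalance afterwards. Demographics come from the questionnaire (Sections 2.10 and 2.11), so people who never click have none, yet they count as not willing in the primary analysis (Section 2.9.1). The primary model adjusts only for residential status (Section 2.12.1).

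**Working it through.** The protocol gives no figure on this point to reproduce, so the check compares its statements and tests what the verification can see.

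**1. Claim against procedure.**
- Claim (2.7.3): platform staff could not get at the sequence before implementation.
- Procedure (2.7.2): two staff with platform access held the list, and one worked down it by hand with identities visible. No masking of later entries and no release of one entry at a time is described.
- Result: at each assignment after the first, the assigner already had the later allocations. Concealment has to hold at every assignment, not only until the list is handed over.

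**2. What the verification can detect.** Within a stratum, let L(k) be the list entry at position k, and let u(k) be the user placed there. The assigned group is A(u(k)) = L(k). The check described asks whether A(u(k)) = L(k) for every k. That is true for any ordering u. The check finds copying errors and departures from the list. It carries no information on how users came to their positions.

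**3. What kind of bias is left.** The strata in Table 3 sum to the full frame: 541 + 1,172 + 3,096 = 4,809. Everyone eligible was assigned, and assignment was finished before any email was sent. Selection into the trial is therefore excluded. Only reordering of users within a stratum, which moves people between arms, remains possible.

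**4. Illustration under assumed values.** None of these inputs is in the documents. Suppose 37.5% of users have a 10% chance of saying yes and the rest 2%, so the mean is 0.375 × 10% + 0.625 × 2% = 5%. Suppose there is no true incentive effect, and that at a given share of positions the assigner swaps two neighbouring users whenever this puts the likelier responder on a financial-incentive position. With the Table 3 strata and blocks of 3, 6 and 9, averages over 100 simulated trials were:

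| Share of positions open to swapping | Financial, % yes | Control, % yes | Difference, points | Mismatches found by the check |
|---|---|---|---|---|
| 0% | 4.99 | 5.02 | −0.03 | 0 |
| 10% | 5.30 | 4.85 | 0.45 | 0 |
| 25% | 5.69 | 4.66 | 1.03 | 0 |
| 50% | 6.33 | 4.34 | 1.99 | 0 |
| 100% | 7.46 | 3.78 | 3.69 | 0 |

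(The last difference is taken before rounding.) The zeros in the final column follow from step 2. The differences assume an assigner who knows each user's propensity exactly, whereas the article mentions only names and email addresses as visible. The table shows that the check is blind to ordering. It does not estimate any bias in this trial.

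**The case against.** The case on the other side is substantial.

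- **The claim is limited in time.** It refers to the period before implementation, and may mean only that staff did not hold the list until assignment began. On that reading the two sections do not flatly contradict each other. But the sentence then says nothing about the assignment period, when concealment matters, and cannot support a concealment claim.
- **Staff are said to have had no discretion.** Allocation ran sequentially and the list was followed exactly. This is the strongest counter-evidence. It is, however, an assertion about keeping to the list and does not say what fixed the order of users.
- **The usual harm is mostly absent.** With the whole frame assigned before mailing, nobody made an enrolment or consent decision in the light of the next allocation. No passage gives staff a reason to favour an arm. This stands and lowers the practical risk considerably.
- **The check is described by example.** Its full scope may be wider, and a fixed order may be recorded in material not shown. If so, one sentence stating it would largely answer the point.

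A reader might infer two stronger things. The first is that selection took place. No passage shows that, and one can speak only of any selection that might have occurred. The second is that the account of the principal researcher contradicts itself. "The randomization sequence was generated by the principal researcher using Sealed Envelope prior to data collection, exported, and stored securely", yet that person is said to have had no access to identifiers "or the allocation list at any point during the assignment process". Producing a list earlier is compatible with not opening it during assignment. The researcher also had no identifiers and assigned nobody, so knowing the list could not have steered anyone. That charge is not made here.

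**Conclusion.** The point holds as a misstatement of what the procedure protected against. Allocation was not concealed from the staff member who assigned, and the verification as described could not reveal any reordering within a stratum. There is no evidence that reordering happened.

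The size of any bias cannot be obtained from the article. It is zero if users were processed in an order fixed before the list was opened. Otherwise it depends on unrecorded behaviour, and because the full frame was assigned before mailing it is confined to steering between arms. The conclusion assumes that Section 2.7.2 describes the procedure as carried out and that no masking of the list was omitted from the article. The text should be corrected and the order checked before analysis. Nothing here calls for a change of design or a new randomization.

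**What to change.** 1. Replace the concealment sentence in Section 2.7.3 with a statement that platform staff applied an open, pre-generated list by hand and that assignment was not concealed from them.
2. In Section 2.7.2, state how the order of users within each stratum was set, by whom, and whether it was fixed before the list was opened. If it was, say that this fixed order, rather than concealment, was the protection.
3. If that order can be recovered, have the second staff member re-apply each stratum list to it before analysis and report the agreement. The order must be the one actually used. Re-applying the list to an arbitrary export, by user ID or sign-up date for example, would show disagreement that means nothing.
4. If the order cannot be recovered, or does not agree, compare the arms within strata on whatever variables the platform holds and report the lack of concealment as a limitation.

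The cost is a slightly less favourable concealment statement and a small check. The check depends on platform records having been kept since the 2024 mailing, which the article does not confirm. The text corrections do not depend on it.
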